## Abstract

**Background:**

Besides the effects of dietary long chain PUFA on circulating endocannabinoids concentrations, the impact of other nutrients on these system is not known and, whether changes in plasma endocannabinoids levels correlated with changes in body composition and biochemical metabolic risk factors in obese individuals, however, still remains to be characterized.

**Methods:**

We will conduct a 2 months’ open label, parallel-group, randomized controlled trial to determine the effect of whey protein supplementation on levels of endocannabinoids, glycemic and lipid profile, inflammatory factors, adipocytokines and body composition in 60 premenopausal obese women on a weight-loss diet.

**Conclusion:**

Due to strong relationship between endocannabinoids level and insulin resistance and obesity, in this trial, we will illustrate the other benefits of weight loss diet on health and metabolic risk factors. Also for the first, the effects of simultaneous weight loss diet and whey protein supplementation on these variables will be determined.

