### Aims and study hypotheses

The primary aim of the current study is to examine the 2-month effects of whey protein supplementation on levels of endocannabinoids, glycemic and lipid profile, inflammatory factors, adipocytokines and body composition in obese women on a weight-loss diet. As a secondary aim, this study will also investigate the associations between changes in endocannabinoids concentrations and other variables. It is also expected that there will be an improvement in investigated variables.

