### Randomization

Eligible subjects will be stratified according to age and BMI randomly assigned to one of two groups: **control** (standard weight loss group, *n* = 30) and **intervention** (whey supplementation weight loss group, *n* = 30).

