### Intervention

All participants will follow a hypocaloric diet of 800 kcal below estimated energy requirements, energy needs is estimated by Mifflin Jeor St equation. Control group will follow a hypocaloric diet of 800 kcal below estimated energy requirements and intervention group will follow a hypocaloric diet of 916 kcal below estimated energy requirements, each of intervention group subjects will receive 30-g whey protein powders daily. The powders will be provided in a sachet form (each sachet containing 30-g whey protein). Each 30 g of the whey protein supplement will be contained 116 kcal, 0.5 g of lipid, 0.4 g of carbohydrate, and 27.5 g of protein. Participants will be instructed to add one sachet to 250 ml cold water and consume immediately, every evening. In control and intervention group the macronutrients percent will be carbohydrate 55%, fat 30% and protein15%. Subjects will be asked to record powder intake and to check compliance, they will be followed by the dietitian via phone calls or SMS, every three days and, powders will be given to the subjects every 15 days. To create a variety in the diet while maintaining the general principles of diet, the same dietitian will give a dietary exchange list and a diet according to their food habits. A trained dietitian will design the energy requirements and macronutrient distribution and the same dietitian will be available to train participants on the diet.

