### Analysis

SPSS version 17 (SPSS Inc., Chicago, IL, USA) will be used for data analysis. All data will be presented as mean ± SD. The percent change of each variable will be also calculated by the formula [(E − B)/B × 100], where E is the end of treatment values and B is the baseline values. The normality of variables will be tested using Kolmogorov- Smirnov test. Independent sample t-test and the paired sample t-test will be applied for comparing parametric continuous data between and within the groups, respectively. Mann-Whitney test and Wilcoxon test will be used to test the differences in asymmetric variables between and within the groups, respectively. To control confounding variables, analysis of covariance (ANCOVA) test were used to determine the differences between the two groups post-intervention, while adjusting for baseline measurements and covariates. A *p* value less than 0.05 will be considered to be statistically significant.

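### The abstract promises to show benefits of the weight-loss diet, but both arms receive the diet, so only uncontrolled before-after tests could bear on that claim

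*Protocol article*

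**What the plan says.** The first sentence of the abstract's conclusion states that "in this trial, we will illustrate the other benefits of weight loss diet on health and metabolic risk factors".

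The body of the protocol asks a different question. The abstract's methods describe a trial "to determine the effect of whey protein supplementation on levels of endocannabinoids, glycemic and lipid profile, inflammatory factors, adipocytokines and body composition" in women who are all on a weight-loss diet. Under Aims and study hypotheses, "The primary aim of the current study is to examine the 2-month effects of whey protein supplementation on levels of endocannabinoids", followed by the other outcome groups.

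Randomization defines two arms of 30: a standard weight-loss group and a weight-loss group that also receives whey. Intervention says that "All participants will follow a hypocaloric diet of 800 kcal below estimated energy requirements". It then sets the whey arm's diet at 916 kcal below requirements, with 116 kcal supplied by the daily sachet.

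Under Analysis, "Independent sample t-test and the paired sample t-test will be applied for comparing parametric continuous data between and within the groups, respectively", with Mann-Whitney and Wilcoxon tests as the counterparts for asymmetric variables. An ANCOVA then compares the two groups after the intervention, adjusted for baseline and covariates. One threshold, p below 0.05, serves them all.

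**The concern.** A trial can support with randomisation only what differs between its arms. Here the diet is common to both, so a statement about its benefits has to rest on change from baseline within an arm. Without a concurrent diet-free group, that change cannot be separated from regression to the mean, season, assay drift or other changes over the two months. Women are enrolled on a BMI of 30 to 40, which makes some regression to the mean plausible.

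Two things are at stake. One is an announced conclusion on the diet that the design cannot carry. The other is a lesser risk to the whey conclusion: within- and between-group tests stand side by side, and nothing says which one decides. A report could then contrast a significant change in the whey arm with a non-significant one in the control arm, which is not a test of whey.

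**Working it through.** The plan gives no figure for this point, so there is none to reproduce. The check has four steps.

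**1. What the randomised contrast contains.**
- Control: diet 800 kcal below requirements, no whey.
- Intervention: diet 916 kcal below requirements, plus 116 kcal of whey.
- Planned net deficit in the whey arm: 916 − 116 = 800 kcal, the same as in the control arm.

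The planned energy restriction therefore cancels in the between-arm difference. The independent t-test, Mann-Whitney test and ANCOVA all estimate the effect of whey on a background of energy restriction, and none estimates the effect of the diet. Of the planned group tests, only the paired t and Wilcoxon tests remain for that.

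**2. How often a paired test would be significant with no diet effect.**
Inputs: n = 30 per arm (Randomization) and a 5% level (Analysis), taken as two-sided. Assumptions not in the documents: a non-diet drift of *d* baseline SDs, a baseline-end correlation *r* of 0.3 to 0.7, and equal SDs at both times. Normal approximation:

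λ = d × √30 / √(2(1 − r)); P(significant) = Φ(λ − 1.96) + Φ(−λ − 1.96)

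Example with d = 0.3 and r = 0.5: λ = 0.3 × 5.477 / 1 = 1.64, so P = Φ(−0.32) + a negligible term = 0.376.

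| Drift (SD) | r = 0.3 | r = 0.5 | r = 0.7 |
|---|---|---|---|
| 0 | 5% | 5% | 5% |
| 0.2 | 15% | 20% | 29% |
| 0.3 | 28% | 38% | 56% |
| 0.5 | 64% | 78% | 94% |

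A significant paired test therefore cannot be attributed to the diet.

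**3. How often the whey arm alone would be significant with no whey effect.**
If whey does nothing, both arms have the same within-arm power *p* (assumed 0.5 to 0.8), and the arms are independent.

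P(whey significant, control not) = p(1 − p)
- p = 0.5: 0.5 × 0.5 = 0.25
- p = 0.8: 0.8 × 0.2 = 0.16

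**4. Where step 3 does not apply.**
Sample size gives anandamide means of 0.297 and 0.209 and SDs of 0.042 and 0.049, read here as before and after weight loss. The change is 0.297 − 0.209 = 0.088.
- r = 0: SD of change = √(0.042² + 0.049²) = 0.0645; standardised change 0.088 / 0.0645 = 1.36.
- r = 0.5: SD of change = √(0.042² + 0.049² − 0.042 × 0.049) = 0.0459; standardised change 0.088 / 0.0459 = 1.92.

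Even at 1.36, λ = 1.36 × 5.477 = 7.4. If such a fall occurred here, the paired test would be significant in both arms almost surely, whatever whey does. The 25% to 16% therefore concerns outcomes with a weaker within-arm response, which the documents do not identify.

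**The case against.** The strongest reply is that the target is one loose abstract sentence, and that illustrate is a soft verb. The methods, primary aim and arms consistently concern whey, no diet hypothesis is stated, and the controlled analysis is already planned, including a baseline-adjusted ANCOVA. Much of this stands. It limits the point to what may be concluded; it does not remove the sentence or say which test decides.

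Four stronger readings are tempting, and the documents do not support them.
- *The whey comparison is compromised.* It is not: between-group tests and ANCOVA address it directly.
- *The plan will judge the diet, or whey, by paired tests.* The analysis section does not say so. The link to the diet sentence is an inference, drawn because no other planned group test could serve that claim.
- *The aims and the rest of the conclusion repeat the diet claim.* The statement that "It is also expected that there will be an improvement in investigated variables" names no arm and no before-after contrast and can be read as the whey hypothesis. The abstract's second concluding sentence, on diet and whey given together, can be read as whey given during a diet.
- *The misleading pattern arises in 50% to 32% of trials.* That is 2p(1 − p), which also counts trials where only the control arm is significant. The pattern that would wrongly favour whey has half that probability.

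It is also fair that changes from baseline have a legitimate use. The secondary aim relates changes in endocannabinoids to changes in other variables, so within-arm change should still be reported.

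**Conclusion.** The point holds in a limited form. The abstract's claim about benefits of the diet cannot be supported by the randomised comparison, and a conclusion on the diet drawn from the paired tests would be unsound. This part follows from the design and needs no assumed numbers.

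The sizes are illustrative. The false-signal rates for the diet rest on assumed drift and correlation, and the 25% to 16% rests on an assumed within-arm power of 50% to 80% with no whey effect. The protocol nowhere argues from significance in one arm and not the other; that risk arises because the tests are left unranked. No change to the arms or the sample size follows from this point.

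**What to change.** - In the abstract's conclusion, remove the statement about benefits of the diet, or label it as uncontrolled and descriptive.
- In the analysis section, state that conclusions rest on the baseline-adjusted between-arm difference (ANCOVA), and that they concern the added effect of whey in women on an energy-restricted diet.
- Report within-arm changes descriptively, as means with 95% CI, and say that they are not evidence for the diet or for whey.

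The cost is a few sentences, with no new data or analysis. The sponsor gives up an uncontrolled claim about the diet.

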**Trial registration:**

Iranian Registry of Clinical Trials IRCT2017021410181N8.

**Electronic supplementary material:**

The online version of this article (10.1186/s12937-017-0294-x) contains supplementary material, which is available to authorized users.

## Background

Endocannabinoids (EC) identified to date are arachidonic acid metabolites, the most widely studied ones being arachidonoyl ethanolamide or anandamide and 2-arachidonoylglyceride (2-AG). These lipid-like substances are enzymatically generated from membrane phospholipid precursors and are thought to act as autocrine/paracrine mediators. Once released, they are rapidly metabolized, anandamide being degraded primarily by fatty acid amid hydrolase, whereas 2-AG is metabolized by monoglyceride lipase [1]. Endocannabinoids act as CB1 and/or CB2 receptor agonists. Classical CB1 and CB2 receptor transmission is coupled through inhibitory G-proteins (Gi/o) to inhibit adenylyl cyclase (i.e., cyclic AMP formation) and calcium channels and activate potassium channels and mitogen-activated protein kinase [1, 2].

In the CNS, endocannabinoids via activation of CB1 receptors increases food intake by modulating the activity of hypothalamic neurons and, subsequently, the release of orexigenic and anorexigenic neuropeptides. Furthermore, CB1 receptor signaling affects reward and reinforcement circuits in the mesolimbic system, leading to a preference for highly palatable food [3]. The CB1 receptor is also present in peripheral organs important in the control of metabolism and activates anabolic pathways, preferring energy storage [4]. In abdominal obesity, the endocannabinoid system (ECS) is generally up-regulated in both central and peripheral tissues, as indicated by high EC. This hyperactive ECS can contribute to further fat accumulation by enhancing food intake as well as by favoring lipogenesis. The endocannabinoid system plays an important role in the regulation of energy homeostasis, specifically of glucose and lipid homeostasis, and represents an important link between obesity and insulin resistance [3–7].

In several studies, obese individuals displayed higher serum levels of EC than lean individuals. Plasma endocannabinoids are higher in obese women compared with obese men and there are a strong association between high plasma EC levels and visceral obesity and metabolic parameters [7–10]. Besides the effects of dietary long chain PUFA on circulating EC concentrations, the impact of other nutrients on these system is not known [8, 9]. Whether changes in plasma EC levels correlated with changes in body composition and biochemical metabolic risk factors in obese individuals, however, still remains to be characterized [11, 12].

One strategy to help retention of muscle mass and increase fat mass loss during energy restriction includes the consumption of dietary protein intake greater than the RDA of 0.8 g/kg/day [13, 14]. Epidemiological studies indicate that the consumption of milk and dairy products is associated with a lower risk of metabolic disorders and cardiovascular diseases. In particular, whey protein seems to induce these effects because of bioactive compounds such as lactoferrin, immunoglobulins, glutamine and lactalbumin. In addition, it is an excellent source of branch chained amino acids. Although studies are conflicting, it has been suggested as an approach for the prevention and treatment of obesity and diabetes in both humans and animals [15]. Given the putative role of whey protein, plasma EC concentration association with visceral obesity and metabolic profile and, due to the effect of whey protein on EC concentration is not clear, we decided to evaluate the effect of whey protein supplementation on levels of endocannabinoids, glycemic and lipid profile, inflammatory factors, adipocytokines and body composition in obese women on a weight-loss diet.

## Methods

### Design

We will carry out a 2 months’ open label, parallel-group, randomized controlled trial. The proposed clinical trial will be held at the Nutritional research center, department of Nutrition, Ahvaz Jundishapur University of Medical Science for 2 months to assess the efficacy of daily whey 30 mg supplementation in obese subjects Figs. 1 and 2.

**Fig. 1 Fig1:**
[figure not shown]
Protocol flow diagram; We will conduct a 2 months’ open label, parallel-group, randomized controlled trial to determine the effect of whey protein supplementation on levels of endocannabinoids, glycemic and lipid profile, inflammatory factors, adipocytokines and body composition in 60 premenopausal obese women on a weight-loss diet

**Fig. 2 Fig2:**
[figure not shown]
Timeline of study; we predicted 17 month for this trial

### Aims and study hypotheses

The primary aim of the current study is to examine the 2-month effects of whey protein supplementation on levels of endocannabinoids, glycemic and lipid profile, inflammatory factors, adipocytokines and body composition in obese women on a weight-loss diet. As a secondary aim, this study will also investigate the associations between changes in endocannabinoids concentrations and other variables. It is also expected that there will be an improvement in investigated variables.

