### Sample size

The sample size was calculated according to the changes in anandamide level, in response to weight loss, based on the study conducted by Mallipedhi et al. [16]. It was calculated considering 95% confidence interval, 80% power (α = 0.05 and β = 0.2), and the related mean and SD of anandamide levels in the mentioned study (μ1 = 0.297; μ2 = 0.209; SD1 = 0.042; SD2 = 0.049). Finally, 30 subjects were recruited for each group.

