### Measurements

A questionnaire about patients’ demographic situations, diseases, and medications, diabetes history and probable supplementations will be recorded at the beginning of the study. Dietary intake will be assessed by 3 days 24-h recall questionnaires (2 week days and 1 weekend day) at the baseline, middle and the end of study. Total energy and macronutrients intake will be calculated by using Nut IV (the Hearst Corporation, San Bruno, CA). To assess physical activity levels the International Physical Activity Questionnaire (IPAQ) will be used at the baseline and the end of study. Anthropometric parameters will be measured after overnight fasting with minimal clothing and without shoes. In all visits (every 15 days), body weight will be measured with the accuracy of 100 g using seca scale. Stature will be measured in a relaxed position using seca stadiometer with accuracy of 0.5 cm. BMI will be calculated as body weight (kg) divided by the square of height(m). Waist circumference will be assessed at above the iliac crest, just below the lowest rib margin at the end normal expiration to the nearest 0.5 cm. TANITA BC-418 body composition analyzer will be used to calculate total body fat and fat percent, fat free mass and fat free mass percent.

At baseline and end of the trial, 10 ml of venous blood samples (2 ml in EDTA- coated sterile tubes and 8 ml in regular tubes) will be collected after 10–12 h overnight fasting. For determination of plasma AEA and 2-AG, the blood in EDTA coated tubes will be centrifuged at 1500 g at 4 °C for 15 min and will be stored at -80 °C. These variables will be quantified by liquid chromatography/in-line mass spectrometry [7]. Regular tubes will be used for biochemical analyses such as determination of glucose, insulin, total cholesterol, HDL-C, triglyceride, adiponectin, leptin, TNF-α and IL-6 in serum. Blood glucose and lipid profile will be determined by enzymatic method with kits from Pars-azmoon (Tehran, Iran). LDL-C levels will be calculated by the Friedewald equation. Circulating insulin will be measured by immunoassay. Homeostasis model assessment – insulin resistance(HOMA-IR) will be calculated by the following formula: fasting glucose(mg/dl) × fasting insulin(μu/ml)/405. ELISA kits will be used to measure serum adiponectin and leptin levels.

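### The primary aim spans 17 to 20 variables, all judged at p<0.05 with none named primary, although the trial was sized on anandamide alone

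*Protocol article*

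**What the plan says.** - **Aims and study hypotheses.** The section begins "The primary aim of the current study is to examine the 2-month effects of whey protein supplementation on levels of endocannabinoids". The sentence runs on through the other domains to the start of the next one: "levels of endocannabinoids, glycemic and lipid profile, inflammatory factors, adipocytokines and body composition in obese women on a weight-loss diet. As a secondary aim". What is then placed at the secondary level is only that "this study will also investigate the associations between changes in endocannabinoids concentrations and other variables". No outcome domain is moved down.
- **Measurements.** The domains become named variables. There are two endocannabinoids ("For determination of plasma AEA and 2-AG") and a serum panel ("determination of glucose, insulin, total cholesterol, HDL-C, triglyceride, adiponectin, leptin, TNF-α and IL-6 in serum"). Lipids gain a derived variable ("LDL-C levels will be calculated by the Friedewald equation"), and HOMA-IR is computed from glucose and insulin. The body composition analyser gives four outputs. Weight, BMI and waist circumference are described as anthropometry.
- **Analysis.** For every variable, a p "value less than 0.05 will be considered to be statistically significant". The section ranks no variable above another.
- **Sample size.** "The sample size was calculated according to the changes in anandamide level". Anandamide is the only variable used, but neither this section nor any other calls it the primary outcome.

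**The concern.** The Aims section and the Sample size section point to different things. One gives six domains equal standing; the other designs the trial around a single analyte. A reader of the results could not tell from this article which comparison decides whether the primary aim was met.

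The 5% in the sample-size calculation is an error rate for one comparison. If a significant result on any listed variable could be reported as meeting the primary aim, the error rate of the main claim is no longer 5%. The variable that carries the claim could then be chosen after the results are known. The open-label design adds to the value of fixing that choice in advance.

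**Working it through.** **1. Count the variables under the primary aim** (from Measurements).

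| Domain | Variables | Number |
|---|---|---|
| Endocannabinoids | AEA, 2-AG | 2 |
| Glycaemic | glucose, insulin, HOMA-IR | 3 |
| Lipid | total, HDL and LDL cholesterol, triglyceride | 4 |
| Inflammatory | TNF-α, IL-6 | 2 |
| Adipocytokines | adiponectin, leptin | 2 |
| Body composition | fat mass, fat %, fat-free mass, fat-free mass % | 4 |
| **Strict total** | | **17** |
| With weight, BMI and waist | | **20** |

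**2. The plan's own figure.** The article states no familywise error rate. Its only related figure is 30 per group, on anandamide: means 0.297 and 0.209, SDs 0.042 and 0.049, α = 0.05, power 80%.

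- Difference = 0.297 − 0.209 = 0.088.
- Pooled SD = √((0.042² + 0.049²)/2) = 0.0456.
- n per group = 2 × ((1.960 + 0.842) × 0.0456/0.088)² = 4.2, so 5 (6 by the exact t-test).

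The stated 30 is not reproduced. That is a separate matter and does not affect this point. What matters here is that the calculation concerns one variable at α = 0.05.

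**3. Independent tests.** Assume no whey effect on any variable and one two-sided between-arm test at 0.05 each (the article does not state sidedness). P(at least one p<0.05) = 1 − 0.95^k.

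- k = 17: 1 − 0.95^17 = 58.2%; expected false positives 17 × 0.05 = 0.85.
- k = 20: 1 − 0.95^20 = 64.2%; expected false positives 20 × 0.05 = 1.0.

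The expected counts do not depend on correlation; the probabilities do.

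**4. Variables tied by definition.**

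- Fat-free mass % is 100 minus fat %, so it repeats the same test with the sign reversed.
- With adult height fixed, the percent change in BMI equals that in weight.
- Fat-free mass is weight minus fat mass.
- HOMA-IR is built from glucose and insulin, and LDL-C from the other lipids.

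Dropping fat-free mass % takes 17 to 16 (56.0%). Dropping it and BMI takes 20 to 18 (60.3%). Dropping HOMA-IR and LDL-C as well from the strict set leaves 14 (51.2%). These figures still treat the remaining tests as independent.

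**5. Correlated tests.** The article gives no correlations, so those below are assumptions. Each entry comes from 200,000 simulated sets of normal test statistics, counting sets with any |Z| > 1.96.

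| Assumed correlation | 17 variables | 20 variables |
|---|---|---|
| Common to all, 0.1 | 57% | 63% |
| Common to all, 0.3 | 49% | 54% |
| Common to all, 0.5 | 39% | 42% |
| Common to all, 0.7 | 27% | 29% |
| Within domain only, 0.5 | 53% | 57% |
| Within domain only, 0.7 | 48% | 51% |
| Within domain only, 0.9 | 40% | 41% |

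The middle scenarios (common 0.3 to 0.5, within domain 0.5 to 0.9) run from 39% to 57%, or about 40–55%. The lowest entry, 27%, is still more than five times the nominal 5%.

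**6. Remedies compared.** One named primary outcome at 0.05 restores 5%. AEA and 2-AG as unadjusted co-primaries would give 1 − 0.95² = 9.75%. Keeping all 20 as primary under Bonferroni means 0.05/20 = 0.0025 per test. At 30 per group the difference detectable with 80% power would then rise from (1.960 + 0.842) × √(2/30) = 0.72 SD to 1.00 SD. Naming one outcome avoids that loss.

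**The case against.** - **Independence is not credible.** This stands. Step 4 shows that some of the variables are functions of others. A reader might infer that a chance positive is more likely than not. That holds under independence for 14 or more variables, but not under several plausible correlations (49% for 17 variables at a common 0.3; 42% for 20 at 0.5). It should not be the headline.
- **Twenty is the upper count.** This also stands. Weight, BMI and waist are presented as anthropometry, while the aim names body composition. The strict count is 17.
- **No passage says that one significant variable makes the trial positive.** Correct. A reader might infer such a rule, but the aim is only to examine effects and the 0.05 threshold is a convention. The probabilities above are therefore conditional on that reading, which the article leaves open.
- **Multiplicity methods may sit in an unseen analysis plan, and the registry may name a primary outcome.** Both are possible, so the lack of an adjustment method is not the finding. The finding rests on what the article does state: a primary aim covering every domain, beside a sample size built on one analyte. A later document that ranked the outcomes would have to depart from that aim.
- **Anandamide is not the only possible choice.** The sizing inputs concern its change with weight loss, and both arms are on a weight-loss diet, so they do not establish a whey effect. Two endocannabinoid co-primaries with α split between them would also fit the stated aim. This is a fair alternative, but it still requires naming the primary outcome.

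**Conclusion.** The point holds in conditional form. The primary aim covers 17 variables (20 with anthropometry), all at p<0.05 and none named primary, while the sample size rests on anandamide. If a significant result on any of them is taken as meeting the primary aim, the chance of at least one false positive with no whey effect is 58–64% under independence. About 40–55% is more realistic under the assumed correlations. These figures take one two-sided test per variable and no true effect on any variable. The exact value depends on correlations that the article does not give, but every scenario examined is far above 5%.

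**What to change.** - Name one primary outcome: the between-arm difference in end-of-trial plasma anandamide, adjusted for baseline by ANCOVA, tested at two-sided 0.05. It is the variable that sized the trial, and ANCOVA is already in the Analysis section.
- Make every other variable secondary or exploratory, reported as an estimate with a 95% confidence interval. State that no efficacy claim rests on their nominal p-values.
- Reword the Aims section to match. Record the change as a dated amendment before the endocannabinoid assays are run, and check that the registry entry agrees.

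**Cost.** No extra patients, visits or assays are needed. Because recruitment is under way, it takes a formal, justified amendment rather than an edit of wording alone. The price is that nominally significant metabolic or body-composition results can no longer be called primary findings.
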